### Study Design and Setting

The SELECT study is a retrospective cohort study with data from 22 hospitals in the Netherlands, including 4 academic and 18 nonacademic hospitals (Figure 2). Other hospitals may be included as the study progresses and we will use routinely collected electronic data from the participating hospitals. The data sets will contain data on hospitalized patients with COVID-19 from the date the first patient was admitted to the hospital in the Netherlands (March 1, 2020) until data transfer (expected May-December 2023). We will use the heterogeneity in therapeutic regimens in time (ie, first, second, and third epidemiological wave), centers (per protocol high-dose corticosteroids or not), and individual patients in the initial databases to address our aims. In a subpopulation of patients, we will use biobank material collected within the Collaboration on Identification, Understanding and Improved Management of patients with infectious diseases study of the Erasmus MC or collected at the Amsterdam University Medical Center (UMC) within the MERMAIDS-ARI, VIS cohort study or the Amsterdam UMC COVID-19 biobank.

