### Patient Selection and Inclusion Criteria

Adult patients (≥18 years) hospitalized with polymerase chain reaction–confirmed COVID-19 or high clinical suspicion of COVID-19 will be included (Figure 3). Pregnant patients and patients receiving corticosteroids for other conditions during or prior to hospital admission are eligible, although a prespecified sensitivity analysis excluding these patients will be performed. Patients who die within 48 hours after admission or patients who object to participate will be excluded from the study. In WP1 and WP4, we will include patients from all SARS-CoV-2 epidemic waves, and in WP2-3, we will include patients from the first and second waves only. Specific inclusion and exclusion criteria for each work package will be applied. In WP1A, patients will be included who are admitted to the ward with a World Health Organization clinical progression scale class of 4-5 [19] (ie, no oxygen or oxygen therapy via a cannula or [non-rebreather] mask). WP1B includes patients who have progressed to the World Health Organization clinical progression scale class of 5-6 (ie, noninvasive oxygen therapy, including conventional oxygen via cannula [non-rebreather] mask, high-flow nasal cannula, noninvasive continuous positive airway pressure, and noninvasive bilevel positive airway pressure) after in-hospital treatment with 10 days of 6 mg per day dexamethasone. The study population for WP2-4 consists of patients admitted to the ICU for a period exceeding 48 hours, who received invasive mechanical ventilation via an endotracheal tube, a tracheostomy, or extracorporeal membrane oxygenation during their ICU stay.

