Regarding WP4, patients are randomly selected and cases will be patients treated with high-dose corticosteroids, whereas controls will be patients who were not treated with high-dose corticosteroids. In WP4a, inverse probability treatment weighting and inverse probability of censoring weights will be used together in a marginal structural model. After we have analyzed the effect of high-dose corticosteroids on mortality and the other outcome measures, we will use this model to determine if the listed biomarkers modify the effect of high-dose corticosteroids on mortality.

In WP4b, we will identify transcriptome features that are differentially altered between cases and controls. Mean transcriptome levels will be compared using an unpaired *t*-test and *P* values will be adjusted for false-discovery rate using the Benjamini-Hochberg procedure. The log_2_ mean fold change of levels between cases and controls will also be calculated for each transcriptome. We will define transcriptome features as those with an adjusted *P* value of <.05 and a >2.0 or <–2.0 log_2_ mean fold change in level.

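### WP4b compares transcripts with an unadjusted unpaired t-test, so differences in site or biobank, epidemic wave or severity can be read as differences tied to high-dose treatment

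*Protocol article*

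**What the plan says.** All places are in the Methods of the protocol article unless stated.

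- **Selection and groups (Statistical Analysis, WP4).** "patients are randomly selected and cases will be patients treated with high-dose corticosteroids"; controls are patients without high-dose treatment. No matching or stratification is attached.
- **Test (Statistical Analysis, WP4b).** "Mean transcriptome levels will be compared using an unpaired" t-test. P values "will be adjusted for false-discovery rate using the Benjamini-Hochberg procedure". A feature is kept if its adjusted P is below .05 and its log2 "mean fold change in level" lies beyond plus or minus 2, that is, more than four-fold.
- **Source of samples (Study Design and Setting).** Biobank material comes from one study at "Erasmus MC or collected at the Amsterdam University Medical Center (UMC) within the MERMAIDS-ARI, VIS cohort study or the Amsterdam UMC COVID-19 biobank".
- **Period (Patient Selection and Inclusion Criteria).** "In WP1 and WP4, we will include patients from all SARS-CoV-2 epidemic waves".
- **Exposure (Study Design and Setting).** "We will use the heterogeneity in therapeutic regimens in time (ie, first, second, and third epidemiological wave), centers" and individual patients. The Discussion adds that treatment is probably allocated by patient characteristics or centre protocol, and calls this prone to bias by indication.
- **Adjustment elsewhere (Statistical Analysis).** The model for determinants of high-dose use forces study centre in. WP1 to WP3 have a long covariate list. WP4a has inverse probability of treatment weights. None of this is carried to WP4b.

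**The concern.** The features that make high-dose use vary (centre, calendar period, patient condition) are also features on which blood expression profiles can differ. Random selection does not break that link: within the sampled patients it reproduces whatever association exists between treatment and site, biobank, wave or severity. An unpaired t-test has no place for a covariate, so any such difference enters the case-control contrast in full.

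False-discovery control is no protection. It limits chance findings among transcripts whose null distribution is correct. Here the null is shifted for transcripts that treatment does not affect.

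At stake is the WP4b feature list, which the Discussion presents as a first step toward personalised corticosteroid therapy. To the extent that features on it reflect where or when a sample was taken, or how ill the patient was, the list would mislead that aim.

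**Working it through.** The article gives no sample size, power or expected feature count for WP4b, so there is no planned figure to reproduce. The check has three steps.

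**1. Size of the bias.** With two sites and no treatment effect, the expected spurious difference in mean log2 level is

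bias = (site shift) × (site A share among cases − site A share among controls).

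For this alone to reach the cut of 2 log2 units, the site shift must be 2 / (difference in share):

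| Site A share, cases / controls | Difference | Shift needed (log2) | Fold |
|---|---|---|---|
| 70 / 30 | 0.4 | 2/0.4 = 5.0 | 32 |
| 80 / 20 | 0.6 | 2/0.6 = 3.3 | 10 |
| 90 / 10 | 0.8 | 2/0.8 = 2.5 | 5.7 |
| 100 / 0 | 1.0 | 2/1.0 = 2.0 | 4 |

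The cut is therefore a real filter, and its strength depends on the imbalance.

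**2. The plan's full rule, simulated with no true effect.** The rule applied is the unpaired t-test, Benjamini-Hochberg adjusted P < .05 and absolute log2 fold change > 2. Assumptions, none of them from the documents: 50 per group; 10,000 transcripts; within-group SD 1 log2 unit; 30% of transcripts shifted by site, with shifts drawn from a normal distribution of mean 0 and the SD shown. Counts are averages per data set, rounded.

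| Site A share, cases / controls | Site-shift SD | False BH hits | Also pass the cut |
|---|---|---|---|
| 50 / 50 | 0.5, 1 or 2 | about 0 | 0 |
| 70 / 30 | 0.5 | about 2 | 0 |
| 70 / 30 | 1 | about 170 | essentially 0 |
| 70 / 30 | 2 | about 1,200 | about 50 |
| 80 / 20 | 0.5 | about 110 | 0 |
| 80 / 20 | 1 | about 1,050 | about 5 |
| 80 / 20 | 2 | about 2,000 | about 300 |
| 90 / 10 | 0.5 | about 500 | essentially 0 |
| 90 / 10 | 1 | about 1,560 | about 45 |
| 90 / 10 | 2 | about 2,300 | about 650 |

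**3. The same data with site as a covariate.** In a transcript-wise linear model with group and site, false Benjamini-Hochberg hits average at most 0.5 of 10,000 in every row, and none pass the cut. The false hits in step 2 therefore come from the omitted site term.

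The simulation uses site as the example. The same arithmetic holds for wave, or for any severity measure that differs between the groups and shifts expression.

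**The case against.** The strongest reply is that the plan's own rule already deals with most of the problem, and much of this stands. At moderate imbalance (70/30) and site-shift SD 1, essentially nothing passes the cut. Sizeable false lists need strong imbalance, large site shifts, or both.

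A reader might go further and compute the rejection rate of a nominal 5% t-test. With a share difference of 20 to 40 points and a shift of 0.5 to 1.0 within-site SD, it runs from 7% at 30 per group to 72% at 100 per group, which suggests an error that grows with sample size. The documents do not support that reading, because the plan does not use a nominal 5% test. At the worst corner of those assumptions (difference 0.4, shift 1 SD) the bias is 0.4 SD, and the standard error is SD × √(2 × 1.25/n), taking the site variance at its maximum of 0.25. The chance of exceeding the fold-change cut is then:

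- SD 1 log2 unit: (2 − 0.4)/0.289 = 5.5 at 30 per group, about 1.5 in 100 million per transcript.
- SD 2 log2 units: (2 − 0.8)/0.577 = 2.1 at 30 per group, about 1.9%. This falls to about 0.36% at 50 and 0.007% at 100.

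In that range the false-feature rate under the plan's rule is small, and it falls as the sample grows.

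Three further limits stand. The documents give no WP4 split of cases and controls by site or wave, and the stated variation in regimens describes 22 hospitals, whereas WP4 material comes from two centres. So confounding is a possibility to guard against, not an established fact. Data Collection does not say which biobanks hold the blood RNA tubes. Sequencing batch and run layout are not mentioned, and an article commonly leaves such laboratory detail to a fuller plan, so nothing is asked about them here.

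The Discussion mentions propensity scores as a general approach but does not tie them to WP4b. Describing the work as exploratory lowers the stakes, but it does not make the unadjusted contrast interpretable.

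**Conclusion.** The point holds as a possibility that the stated analysis cannot exclude. WP4b fixes a comparison that cannot separate high-dose treatment from site/biobank, wave or severity, in a study that relies on treatment varying along those lines and that adjusts for such factors in its other analyses. Benjamini-Hochberg does not help. The four-fold cut removes most small and moderate artefacts but leaves large ones and those under strong imbalance.

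On the stated assumptions, the number of false features passing the full rule ranges from essentially none (70/30, site-shift SD 1) through about 5 to 45 (80/20 to 90/10, SD 1) to about 300 to 650 (80/20 to 90/10, SD 2), out of 10,000 transcripts. Where the real study falls in that range cannot be read from the article. A reader might infer that the WP4b list will be dominated by site or period effects; the documents do not show that. The change is worth making because the weakness is built into a stated method and a better one costs little.

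**What to change.** In the WP4b paragraph, replace the unpaired t-test with a transcript-wise linear or count model containing group, site/biobank, wave, age, sex and severity at sampling; alternatively, carry over the treatment weights already planned for WP4a. Draw controls within site/biobank and wave where the stored samples allow it. Keep the Benjamini-Hochberg step, and apply the fold-change cut to the adjusted estimate instead of the raw mean difference.

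The cost is a change of analysis wording, a stratified draw from samples already stored, and a few degrees of freedom. Strata holding only cases or only controls contribute nothing to the adjusted contrast. If site and treatment coincide completely, no adjustment can separate them, so the case and control counts by site/biobank and wave should be reported beside the feature list.

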## Results

The study was funded in December 2021. As of April 2023, data have been collected for a total of 1500 patients, with data collection anticipated to be completed by December 2023. We expect the first results to be available in early 2024.

## Discussion

The SELECT study is a retrospective multicenter observational cohort study that aims to determine the most optimal dosing and timing of high-dose corticosteroid therapy in hospitalized patients with COVID-19 and to provide a basis for personalized treatment regimens using biomarkers and whole transcriptome analyses. Increasing insight in the pathophysiological pathways that underlie SARS-CoV-2 infection and the efficacy of high-dose corticosteroid therapy could lead to more precise targeting of high-dose corticosteroid therapy, and as a result, could improve patient outcomes.

The necessity of exploring this matter is underlined by the fact that there is currently no consensus regarding the administration of high-dose corticosteroid therapy in patients with COVID-19.

This study design has several strengths. First, no studies have been performed that evaluate the effect of high-dose corticosteroids throughout the entire clinical course of hospitalized patients with COVID-19. Our study will evaluate the effect of high-dose corticosteroids from hospital admission to the ward or ICU, until hospital discharge. Furthermore, our exploration of biomarker and gene expression profiles for targeted corticosteroid therapy represents a first step toward personalized corticosteroid therapy in COVID-19. By using existing research databases and biobanks, successful data collection is assured, and we will be able to include a large number of patients, which increases the generalizability of the results.

Due to the retrospective study design, some methodological considerations require further discussion. A major issue for any observational study is the fact that treatment modalities are not randomly assigned, but rather likely given based on specific patient characteristics or within-center protocols. This nonrandomized assignment is prone to bias by indication. To correct this bias, our initial analysis step will be the identification of factors that contribute to the allocation of corticosteroid treatment. Subsequently, we will examine several statistical approaches, such as the use of propensity scores at the patient level to minimize treatment indication bias.

The findings of this study could support COVID-19 guidelines and hospital protocols regarding the management of hospitalized patients with COVID-19. Thus far, the translation of predictive biomarkers and whole transcriptome analysis into an applicable bedside tool is highly challenging. We expect to provide valuable tools to guide the dosing and timing of high-dose corticosteroid therapy. Furthermore, the answers to our research questions might be extrapolated to patients with non–COVID-19 ARDS, as the use of high-dose corticosteroids is still a matter of debate in this group of patients. The mortality rate of non–COVID-19 ARDS is even higher than that of COVID-19 ARDS [24], emphasizing the need for improved treatment strategies. Nonetheless, more efforts are required to determine similarities and differences between patients with COVID-19 ARDS and those with non–COVID-19 ARDS to determine whether extrapolation from one group to the other is possible.

In conclusion, our study protocol presents a strategy to gain a better understanding of the optimal dosing and timing of high-dose corticosteroid therapy in hospitalized patients with COVID-19 and thereby improve patient outcomes.

## Appendix

Multimedia Appendix 1 Definition of general systemic complications.

Multimedia Appendix 2 Peer-review report by the COVID-19 Program - The Netherlands Organisation for Health Research and Development / ZorgOnderzoek Nederland (ZON) and the area Medical Sciences (MW) (ZonMw, Netherlands).

## Abbreviations

ARDS: acute respiratory distress syndrome
BALF: bronchoalveolar lavage fluid
ICU: intensive care unit
SELECT: Steroids in Hospitalized Patients with COVID-19 in The Netherlands
UMC: University Medical Center
WP: work package
